## Introduction

### Adult Weight Management

Small weight gains over time, around 1-2 pounds per year [1,2], contribute to the development of overweight and obesity. Once established, obesity is difficult to treat [3], as reduction of excess body weight is rarely effective in the long term. Short-term weight loss can be achieved by a variety of methods, but few of these approaches are sustainable and effective in facilitating permanent weight loss [4-10]. On average, individuals adhere to weight loss programs for approximately six months [11]; following weight loss, most individuals regain half of the weight lost within one year, and return to baseline weight within 3-5 years [11-13]. Weight gain prevention, on the other hand, avoids the difficulties that may accompany weight loss and its maintenance and offers an alternative option for weight management.

To reduce disease risk and improve overall health, effective weight gain prevention is essential; however, few interventions have successfully examined weight gain prevention and little is known about the determinants of and strategies for preventing weight gain over the long term. Much of the existing research has focused on treatment of overweight and obesity through reduction of excess body weight [14,15] or prevention of weight regain following weight loss [16-20].

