### Aims and Objectives

The current study aims to identify determinants of weight gain prevention in young adult and midlife premenopausal women through a 1-year weight gain prevention intervention that includes nutrition education. We hypothesize that compared to a wait-list control group, women who participate in a weight gain prevention intervention designed to increase self-efficacy, self-regulation, outcome expectations, and family and social support will maintain current body weight during a 12-month period. It is further hypothesized that women in an intervention group led by registered dietitians will have less weight gain during 12 months compared to women in an intervention group led by counselors.

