### Statistical Analysis

Baseline characteristics of study participants were characterized using descriptive statistics: mean (SD). Participants in the three intervention groups (Treatment) will participate in five data collection sessions at specified intervals (Time). The Shapiro-Wilk test for normality will be used to test for normality and homogeneity of variance within groups; data will be transformed if necessary. Body weight, BMI, waist : hip ratio, FM, BF%, systolic and diastolic blood pressure, serum insulin, glucose, TC, HDL-C, LDL-C, TG, leptin, adiponectin, and resistin will be analyzed as dependent variables. Baseline variables that differ between groups will be included as covariates in the analysis. Dietary intake of macronutrients as estimated from 4-day food records, estimated energy expenditures, eating behaviors, health perceptions, and ratings of SCT mediators also will be compared among groups. A 3 x 5 (3 treatment groups x 5 time intervals) ANOVA with repeated measures on the time factor will be used to assess differences in outcomes within and between treatment groups over time. The group by time interaction will be examined for differences in time trend among intervention groups. Tukey pairwise comparisons will be used in conjunction with ANOVA to detect differences between treatment groups.

Some attrition is expected, as participants may be unable to comply with the intervention or may choose not to continue participation in the study. Participants who withdraw from the intervention will be asked to complete any remaining data collection sessions, and these data will be included in the statistical analyses (ie, intention-to-treat model). Data also will be analyzed using measurements only from those participants who complete all testing sessions. Statistical tests will be two-tailed with significance set at *P*<.01 to reduce the potential for Type I error. All statistical analyses will be conducted using Statistical Package for the Social Sciences (version 22.0, 2013, IBM Corp, Armonk, NY, USA).

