In a recent qualitative study of women who completed a weight-loss intervention conducted by a registered dietitian, women perceived the registered dietitian to be a credible source of nutrition information and found lack of access to a registered dietitian following completion of the intervention to be a barrier to weight-loss maintenance [29]. As a credible source of nutrition information [37], registered dietitians have a specialized skill set to support and encourage sustainable behavior changes to achieve weight management. Registered dietitians are generally regarded as the experts in weight management, but no studies have compared registered dietitians to other health professionals in the delivery of weight management information. The current study will fill this scientific gap by testing the ability of the registered dietitian to promote weight gain prevention as compared to an untrained professional. If registered dietitians are more effective in promoting weight gain prevention, these findings will support the notion that registered dietitians should be at the forefront in helping individuals attain successful weight management.

Women in the qualitative study [29] identified social support, basic nutrition education, accountability to others, self-motivation, mindfulness and awareness of food choices, planning ahead, portion control, and exercise as facilitators to weight loss and weight-loss maintenance while health status changes, environmental pressures, life transitions, absence of social support, lack of accountability, and internal factors were perceived as barriers. Additionally, women expressed their desire for continual contact with the registered dietitian as well as the group support offered by the education sessions [29].

Although there is no standardized definition of weight gain prevention or weight maintenance, a weight change of ±3% from baseline weight will be considered successful weight gain prevention. A 3% change criterion allows for normal day-to-day fluctuations that may result from measurement error, clothing, food consumption, and/or fluid balance [54].

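### The maintenance part of the first hypothesis has no analysis that could support it: the within-group ANOVA tests for change, and the article's own ±3% criterion is not used in any planned analysis

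*Protocol article*

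**What the plan says.** **Hypothesis (Protocol article, Aims and Objectives).** The first hypothesis opens with a comparator: "We hypothesize that compared to a wait-list control group, women who participate in a weight gain prevention intervention designed to increase self-efficacy" and three further constructs "will maintain current body weight during a 12-month period". It thus contains a comparison with wait-list control and a prediction that weight is maintained. The second hypothesis, dietitian versus counselor, is worded purely as a difference in weight gain.

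**Analysis (Methods, Statistical Analysis).** A 3 x 5 design is specified: "ANOVA with repeated measures on the time factor will be used to assess differences in outcomes within and between treatment groups over time". Between groups, "The group by time interaction will be examined for differences in time trend among intervention groups", and "Tukey pairwise comparisons will be used in conjunction with ANOVA to detect differences between treatment groups". On the level, "Statistical tests will be two-tailed with significance set at" P<.01, a choice justified by concern about Type I error.

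**Criterion (Discussion, Principal Findings).** The article says that "a weight change of ±3% from baseline weight will be considered successful weight gain prevention". The Statistical Analysis section does not mention this criterion.

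**Expected gain (Introduction, Adult Weight Management).** The drift to be prevented is described as "Small weight gains over time, around 1-2 pounds per year".

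**The concern.** Maintenance in an arm is a claim that its mean weight did not change by a relevant amount. A repeated-measures ANOVA takes no change over time as its null hypothesis. Rejecting it shows change; failing to reject shows only that change was not detected. Used as evidence of maintenance, the test rewards imprecision: a stricter alpha, more variable weights and more dropouts all make non-significance more likely. P<.01 protects against false claims of difference but gives no protection against a false claim of no change.

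The article already holds the missing piece, a numerical limit for successful prevention, but leaves it in the Discussion without an analysis. What is at stake is how the 12-month result for each intervention arm is described. An arm that gained weight at the rate the trial wants to prevent, or even by a mean of 3%, could be reported as having maintained weight on the strength of a non-significant time effect.

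**Working it through.** The article states no sample size or power calculation, so there is no figure of its own to reproduce.

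**Inputs from the article**
- Women with baseline data: 81 (Results). At week 8, 49 women, given as 89%, remained in the two intervention groups. 49/0.89 ≈ 55 at baseline, so 55/2 ≈ 27 per intervention arm. This agrees with 81/3 = 27. The control arm is then 81 − 55 = 26. At week 8, 49/2 ≈ 24 remained per intervention arm.
- Mean baseline weight: 76.1 kg (Table 1). The 3% limit is 0.03 × 76.1 = 2.28 kg.
- Expected gain: 1 to 2 lb per year, or 0.45 to 0.91 kg. As a share of baseline, 0.91/76.1 = 1.2%.
- Alpha: .01, two-sided.

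**Assumption.** The SD of 12-month weight change is not given. The 19.0 kg in Table 1 is the spread between women, not of change. A range of 3 to 6 kg is used.

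**Step 1: how often a real gain is non-significant.** For a paired baseline-to-12-month test, the noncentrality is λ = δ√n/σ and the miss rate is P(|T| < t_crit), with T noncentral t on n − 1 df. For n = 27, t_crit = 2.779 at P<.01. Example: δ = 0.91, σ = 3 gives λ = 0.91 × 5.196/3 ≈ 1.57 and a miss rate of 86%.

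| Assumed SD of change (kg) | 0.91 kg gain, n = 27 | 2.28 kg gain, n = 27 | 2.28 kg gain, n = 24 |
|---|---|---|---|
| 3 | 86% | 13% | 19% |
| 4 | 93% | 42% | 49% |
| 5 | 95% | 64% | 69% |
| 6 | 97% | 77% | 80% |

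A gain of 0.45 kg is missed 96.7% to 98.5% of the time (n = 27). Without any assumed SD, a gain of half an SD is missed 56% of the time with n = 27 and 62% with n = 24.

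**Step 2: does the five-visit ANOVA behave differently?** Two simulations of a one-arm, five-visit time test at P<.01 (n = 27, Greenhouse-Geisser correction) used different covariance models. With random linear slopes plus visit error, 0.91 kg was missed 83-95% of the time and 2.28 kg 11-61% (SD 3 to 5 kg). With random-walk weights, 0.91 kg was missed 87% (SD 3) and 95% (SD 5), and 2.28 kg 12% and 63%. The paired-test figures are a fair guide.

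**Step 3: what a rule based on the article's ±3% would do.** Call an arm maintained only if its two-sided 95% CI for mean change lies wholly within ±2.28 kg. The half-width is t_.975 × s/√n, with t_.975 = 2.056 for n = 27. The probability that the CI fits is the normal probability that the mean lies within ±(2.28 − half-width), averaged over the chi-square distribution of s².

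| Assumed SD of change (kg) | True change 0 | True gain 0.91 kg | True gain 2.28 kg |
|---|---|---|---|
| 3 | 93% | 63% | 2.5% |
| 4 | 63% | 38% | 2.5% |
| 5 | 27% | 18% | 2.1% |
| 6 | 7% | 5% | 1.0% |

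The rule holds the false claim at a true 3% gain to 2.5% or less, against 13-77% if non-significance were taken as maintenance. It does not exclude a 2 lb gain, because 0.91 kg lies well inside the limit.

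**The case against.** Four points deserve weight.

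**The hypothesis is comparative.** A reader might infer that the first hypothesis as a whole goes untested. The article does not support that. It names wait-list control as comparator, and the group-by-time interaction and Tukey comparisons are difference tests of the right kind for that part. For the same reason it cannot be said that the trial has no means of separating prevention from no prevention. Whether the comparison has enough power is a separate question. This objection stands and limits the point to the maintenance part.

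**The article never says that a non-significant time effect means maintenance.** That is correct. Such a reading is a risk the plan leaves open, not a rule it states, and the miss rates above describe what would follow if it were adopted.

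**A definition of maintenance exists.** Also correct: the ±3% criterion does not depend on a P value, and the proportion of women meeting it would be an arm-level result. The defect is that no planned analysis uses it.

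**The article is condensed, and the figures describe a test it does not literally name.** Details of confidence intervals and responder analyses are often left to a fuller plan. But this section does fix the model, post-hoc test, level, sidedness, analysis sets and software, and the within-group test it fixes does not fit the wording of the hypothesis. That is a mismatch between two stated elements. On the figures, the planned model has three arms; pooling error across them (78 df) changes the miss rates for a 2.28 kg gain only to 10%, 37%, 60% and 74% for SD 3, 4, 5 and 6 kg.

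**Conclusion.** The point holds for the maintenance part of the first hypothesis only. No analysis in the Statistical Analysis section can support a statement that an arm maintained weight, and the criterion that could do so is not connected to any analysis. With about 27 women per arm at P<.01, non-significance would say little: a 0.91 kg mean gain would go undetected 86-97% of the time and a 2.28 kg gain 13-77%. The arm size is derived from the article. The ranges rest on the assumed SD of change of 3 to 6 kg, and the 3% limit is converted to kg at the mean baseline weight. The conclusion that non-significance cannot establish maintenance does not depend on that SD. This is an inexpensive improvement to the analysis text, and the comparison with control is unaffected.

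**What to change.** Add to the Statistical Analysis section:

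- A non-significant time effect will not be taken as evidence of weight maintenance.
- Each arm's mean 12-month weight change, in kg and as a percentage of baseline, will be reported with a two-sided 95% CI. An arm will be described as having maintained weight only if that CI lies wholly within ±3%.
- The proportion of women within ±3% of baseline will be reported by arm.
- The intervention-minus-control difference in 12-month change, with its CI, remains the test of benefit.
- Because +3% is wider than the expected yearly gain, each arm's CI will also be shown against 0.45 to 0.91 kg, and lying within ±3% will not by itself count as evidence of prevention.

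The limit should stay two-sided, as in the article; an upper limit alone would let an arm with large weight loss count as maintained.

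**Cost.** A few sentences; no new data, visits or participants. The downside is that maintenance becomes harder to claim. With n = 27 and a true change of 0, the CI lies within ±2.28 kg only about 93%, 63%, 27% and 7% of the time for SD 3, 4, 5 and 6 kg, so some truly stable arms would be reported as inconclusive. A 99% CI, to match the P<.01 level, would lower these to 74%, 22%, 2% and 0.2%, so the text should state that the interval is set at 95%.

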### Study Design

The current study is a 12-month parallel-arm weight gain prevention randomized controlled trial. After enrollment, women were randomized to one of three intervention groups: (1) weight gain prevention intervention delivered by a registered dietitian (RDG); (2) weight gain prevention intervention delivered by a counselor (CSG), or (3) wait-list control (CON) group. The RDG and CSG weight gain prevention interventions are identical in materials and content; the only difference is the credentialing of the individuals leading the intervention. Women in the CON group receive no intervention; upon completion of the 12-month waiting period, these women will be randomized to the RDG group or CSG group and will receive the respective intervention for the next 12-month period.

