### Outcome Measures

Before the intervention (baseline), data on dietary intake, physical activity, anthropometric, and blood pressure measurements, biochemical markers of health, eating behaviors and health perceptions, and SCT mediators of behavioral change were collected. These outcome measures also will be obtained at 3, 6, 9 and 12 months.

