## Results

Eighty-one women completed baseline testing. Baseline descriptive characteristics of the sample are displayed in Tables 1 and 2. Overall, these women were highly educated, with a majority of participants having at least a 4-year college degree. The racial/ethnic breakdown was reflective of the larger population, with non-Hispanic whites representing the majority. Age range was 18-45 years, and BMI range was 18.5-49.6 kg/m^2^. On average, participants were overweight and normotensive. Participants have been recruited, enrolled, and randomized to one of the three intervention groups. Education sessions will continue through August 2015, and results are expected by early 2016.

After 8 weeks, the halfway point for weekly education sessions, 75 (93%) of the original sample remained in the study. For those randomized to the two intervention groups, 49 (89%) women were still enrolled.

**Table 1 table1:** Baseline characteristics of women (n=81) participating in a 12-month weight gain prevention intervention and completing baseline testing.

Characteristic	All participants mean (SD)
Age (years)	31.4 (8.1)
Height (cm)	165.2 (5.9)
Weight (kg)	76.1 (19.0)
Body mass index (kg/m^2^)	27.9 (6.8)
Waist circumference (cm)	83.3 (13.6)
Hip circumference (cm)	110.7 (14.6)
Waist: hip ratio	0.8 (0.1)
Body fat (%)	34.6 (9.1)
Fat mass (kg)	27.9 (14.2)
Fat free mass (kg)	48.2 (5.4)
Systolic blood pressure (mmHg)	106.2 (11.0)
Diastolic blood pressure (mmHg)	70.9 (9.9)
Resting heart rate (bpm)	65.8 (6.0)

**Table 2 table2:** Demographic and education characteristics of all women (n=81) randomized to all groups.

Characteristic		All participants No (%)

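### All losses to week 8 are in the led arms, before any follow-up weight, and the article describes no lighter contact that would still obtain a weight

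*Protocol article*

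**What the plan says.** Statistical Analysis foresees two kinds of attrition: "participants may be unable to comply with the intervention or may choose not to continue participation in the study". For the first kind it states "Participants who withdraw from the intervention will be asked to complete any remaining data collection sessions", and it includes the resulting data under intention to treat. It adds a completers analysis: "Data also will be analyzed using measurements only from those participants who complete all testing sessions". The model is "A 3 x 5 (3 treatment groups x 5 time intervals) ANOVA with repeated measures on the time factor".

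Outcome Measures lists the full set of assessments at baseline and then says "These outcome measures also will be obtained at 3, 6, 9 and 12 months". The following sections describe that set: a 4-day food record, a 7-day activity record (with an accelerometer for about 70% of each group), anthropometry and blood pressure, about 30 mL of blood after a 12-hour fast, and several questionnaires. No reduced visit is described, and none is ruled out.

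Study Design says of the wait-list arm: "Women in the CON group receive no intervention". Results gives week-8 retention as 75 (93%) of the sample overall, and then: "For those randomized to the two intervention groups, 49 (89%) women were still enrolled". It does not say whether the women no longer counted had stopped sessions only or had also left measurement.

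**The concern.** Body weight over 12 months is the outcome in both hypotheses (Aims and Objectives). A woman who has given up weekly classes may decline a fasting blood draw and several days of records, yet might agree to be weighed. If no such option is offered, her weight may be lost along with everything else.

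The early losses fall on one side of the led-versus-control comparison. If women who leave a weight program tend to gain more than those who stay, which is plausible but not shown here, missing their weights flatters the led arms. No analysis can recover a weight that was not taken. Because Results does not separate stopping sessions from leaving follow-up, a reader cannot tell whether the intention-to-treat rule is reaching these women.

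**Working it through.** **Inputs.** 81 women with baseline testing; 75 (93%) remaining at week 8; 49 (89%) remaining in the two led arms (Results). First follow-up measurement at month 3 (Outcome Measures). Usual gain of 1–2 lb per year (Introduction, Adult Weight Management). Mean baseline weight 76.1 kg (Table 1). Success defined as ±3% of baseline weight (Discussion, Principal Findings).

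**1. Reproduce the stated percentages.** 75/81 = 92.6%, which rounds to 93%; 81 is the only whole-number denominator that fits (75/87 would be 86%). 49/55 = 89.1%, which rounds to 89%; 55 is the only fit.

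**2. Control arm by subtraction.** Baseline: 81 − 55 = 26. Week 8: 75 − 49 = 26.

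| | Baseline | Week 8 | Lost |
|---|---|---|---|
| Led arms | 55 | 49 | 6 (10.9%; exact 95% CI 4.1% to 22.2%) |
| Control | 26 | 26 | 0 (exact 95% upper limit 13.2%) |

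The split of the six between dietitian and counselor arms is not given. A different six women (87 − 81) were randomized but have no baseline testing; their arms are not stated either.

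**3. Could this be chance?** If loss were unrelated to arm, the probability that all six fall in the led arms is C(55,6)/C(81,6) = 0.089. The two-sided Fisher exact p is 0.17. Chance is a reasonable explanation.

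**4. Timing.** Week 8 comes before month 3, so the six contribute no post-baseline weight unless they return.

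**5. Possible bias.** Let stayers change by m kg on average and leavers by m + d. The full led-arm mean is (49m + 6(m + d))/55 = m + (6/55)d. Using stayers only understates it by 0.109d. The documents give no value for d, so it is an assumption:

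| d (kg) | Shift in led-arm mean (kg) |
|---|---|
| 1 | 0.11 |
| 2 | 0.22 |
| 3 | 0.33 |
| 5 | 0.55 |

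If d is negative, the bias reverses.

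**6. Scale at d = 2.** 1–2 lb is 0.454–0.907 kg; 0.218/0.907 = 24% and 0.218/0.454 = 48% of the yearly gain to be prevented. Against the success margin, 3% of 76.1 kg = 2.28 kg, and 0.218/2.28 is about 10%.

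**7. The ±3% classification, with no assumption about d.** If s of the 49 stayers succeed, the led-arm proportion lies between s/55 and (s + 6)/55, a range of 6/55 = 10.9 percentage points.

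**8. Would a late weight be used?** A conventional 3 x 5 repeated-measures ANOVA uses only women with all five measurements. In that form a woman weighed at month 12 alone would not enter it, and the intention-to-treat analysis would move toward the completers analysis.

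**The case against.** The plan already does the main thing expected of it: it seeks data after withdrawal and analyzes them. Much of the case against it would rest on silence, and several stronger readings are tempting but unsupported.

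- *A leaver must take the full battery or nothing.* A reader might infer this, but the text says only data collection sessions. The battery is not all-or-nothing even for participants, since about 30% wore no accelerometer, and a condensed article may omit a reduced visit that the full protocol contains.
- *Control women who leave are not followed.* Read literally, the rule covers withdrawal from an intervention that control women do not receive. But the article elsewhere counts control among its three intervention groups and schedules all three for five sessions. This is loose wording, not a separate rule.
- *The week-8 count contradicts the follow-up rule.* The six may be women who chose to leave the study, a kind of attrition the plan foresees. An enrollment count is not a follow-up rule.
- *Weight will be lost in the led arms only.* This extrapolates eight weeks to twelve months. Control women can also leave, and 0 of 26 is compatible with a loss of up to about 13%.
- *Both hypotheses are biased.* The dietitian versus counselor comparison suffers only if loss differs between those two arms, and that split is not reported.

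These points stand and limit the claim. They leave intact the counts, their timing before any follow-up weight, the undivided reporting of who left, and the absence of any described contact that protects weight alone.

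**Conclusion.** The point holds as a risk with a cheap safeguard, not as a demonstrated error. By the article's own figures, losses to week 8 are 6 of 55 in the led arms against 0 of 26 in control, so weight may be lost unequally between the led arms and control. No missing weight is yet shown.

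The size of any bias in the led-arm mean is 0.109d kg. It rests on three assumptions: the leaver–stayer gap d and its sign, that none of the six returns, and that control loses nobody. The figure covers only the first eight weeks of losses.

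**What to change.** Reword the attrition paragraph in Statistical Analysis so that any participant in any arm who stops sessions or leaves the waiting list stays in follow-up unless she withdraws consent for data. If she declines a full session, offer a weight-only visit on the study scale at each remaining time point, with month 12 as the priority.

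Bring these weights in through an analysis that keeps women with incomplete visits, such as a mixed model for repeated measures, and use them in the ±3% classification at month 12. Offer the same to the six early leavers where consent allows. In reporting, separate women who stopped the intervention but are still followed from those who withdrew consent or were lost, by arm.

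The cost is a short IRB amendment and a few brief weighings with the existing scale. Other outcomes would remain missing for weight-only visits.

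### The repeated-measures ANOVA named for the intention-to-treat analysis needs all five visits, so it would reduce to the completers analysis and discard partial data

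*Protocol article*

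**What the plan says.** All of the analysis commitments are in the Statistical Analysis section of the protocol article.

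- **Visits.** Women "will participate in five data collection sessions at specified intervals (Time"). Outcome Measures sets these at baseline and 3, 6, 9 and 12 months.
- **Model.** "A 3 x 5 (3 treatment groups x 5 time intervals) ANOVA with repeated measures on the time factor will be used" for differences within and between groups. No mixed model, other likelihood method or imputation is named.
- **Withdrawals.** "Some attrition is expected, as participants may be unable to comply with the intervention or may choose not to continue participation". Women who withdraw are to be asked to attend the remaining sessions, and "these data will be included in the statistical analyses (ie, intention-to-treat model").
- **Second analysis.** "Data also will be analyzed using measurements only from those participants who complete all testing sessions".
- **Software.** "All statistical analyses will be conducted using Statistical Package for the Social Sciences", version 22, with no procedure named.

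The Results section gives retention at 8 weeks: 75 (93%) of the original sample, and "For those randomized to the two intervention groups, 49 (89%) women were still enrolled".

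**The concern.** The article describes two analyses that are meant to differ. One includes whatever is measured on women who withdraw, and the other is limited to women with every session. The model named cannot make that distinction. A classical repeated-measures ANOVA takes one record per woman with a value at each level of the time factor, and a record with a gap is deleted whole. A woman who withdraws, misses months 6 and 9 and returns at month 12 would lose her 12-month weight from the analysis, although the plan says that her data will be used.

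The trial could therefore report a completers comparison under an intention-to-treat label. The first hypothesis compares intervention with wait-list control over 12 months, and one reason the plan gives for attrition is inability to comply with the intervention. Controls receive none during the waiting year, so that reason cannot apply to them. This is the setting in which a completers comparison can mislead and in which the intention-to-treat analysis is supposed to give protection.

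**Working it through.** **1. Do the two analysis sets differ?** Take a woman's record over the five visits for one outcome, such as body weight.

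| Record | Kept by classical 3 x 5 ANOVA | In the completers set |
|---|---|---|
| Stays in the intervention, all five visits | yes | yes |
| Withdraws, attends all five visits | yes | yes |
| Withdraws, misses at least one visit | no | no |
| Stays in the intervention, misses at least one visit | no | no |

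The columns agree in every row, because both require five values. This follows from the definitions and needs no assumption about dropout. The analyses separate only if some unstated method handles incomplete records.

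**2. The plan's own retention figures.**

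- Overall: 75/81 = 92.6%, reported as 93%. The figure reproduces.
- Intervention arms: the denominator is not printed. 49/54 = 90.7%, 49/55 = 89.1% and 49/56 = 87.5%, so only 55 gives the reported 89%.
- Control, by subtraction: 81 - 55 = 26 at baseline and 75 - 49 = 26 at week 8. This assumes that both percentages use the baseline-tested sample.

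Enrolment losses from baseline to week 8 are therefore 55 - 49 = 6 of 55 (10.9%) in the intervention arms and 0 of 26 in control.

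**3. How strong is that imbalance?** If the six losses were unrelated to arm, the chance that all fall among the 55 is C(55,6)/C(81,6) = 0.089. Fisher's exact two-sided P for 6/55 against 0/26 is 0.17.

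**4. How many women could the ANOVA use?** The document gives no final dropout or missed-visit rate, so these are illustrations. Let d be the proportion who drop out, each missing at least one session, and let p be the chance that any other woman misses a given follow-up, independently over the four follow-ups. The retained share is (1 - d)(1 - p)^4.

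| d | p | Share retained | Of 81 |
|---|---|---|---|
| 0.10 | 0.03 | 0.90 x 0.885 = 0.797 | about 65 |
| 0.20 | 0.05 | 0.80 x 0.815 = 0.652 | about 53 |
| 0.30 | 0.10 | 0.70 x 0.656 = 0.459 | about 37 |

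With no dropout at all, occasional missed visits at 3%, 5% or 10% would still leave only about 72, 66 or 53 of 81.

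**The case against.** **The article never says that incomplete records are dropped.** Deletion is a property of the classical method and of SPSS GLM repeated measures. SPSS also has a MIXED procedure, and the wording shows that two different analyses were intended. Handling of missed visits is often left to a fuller document. All of this is fair, and it would be wrong to say that the plan decides to discard these women. But the article does fix the model, the label and the second analysis set, and under the usual meaning of the model they do not fit together. That is a conflict in what is stated, beyond a missing detail.

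**The week-8 counts are not missing outcomes.** This stands. They are enrolment counts, the first follow-up measurement is at 3 months, and women who withdraw are to be asked to keep attending.

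**The imbalance may be chance, and it is incomplete.** This also stands. There are six events, with P = 0.17, and about ten months remained in which controls could leave. Recruitment, Screening, and Enrollment shows six further women lost between randomization (87) and baseline testing (81), and their arms are not given.

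**A reader might infer that the intervention arms are already selected and that the comparison is biased in favour of the intervention.** The documents do not support this. They give no weight data on women who left, so neither the presence nor the direction of bias can be read from them.

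**A mixed model may not rescue the women at issue.** With baseline only as a covariate and post-baseline values as outcomes, a woman with no follow-up visit is still omitted. This is correct, and the fix below allows for it.

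**Conclusion.** The point holds in a limited form. As written, the model named for the intention-to-treat analysis would yield the completers analysis for each outcome and discard observed data from any woman with a missed visit. This rests on one assumption: that the repeated-measures ANOVA is run in its classical form, which is the plain reading of the text.

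The size cannot be fixed from the document. The 80% to 46% range depends wholly on assumed rates and on every dropout missing at least one session. It shows what could happen and does not forecast this trial. If every withdrawn woman attended all sessions and nobody else missed one, nothing would be lost.

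The week-8 split of 6 of 55 against 0 of 26 is a reason to take attrition by arm seriously. It does not establish an arm effect, lost outcome data or a direction of bias.

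**What to change.** For the intention-to-treat analysis, replace the repeated-measures ANOVA with a likelihood-based linear mixed model with treatment-by-visit effects, using every observed measurement by randomised arm. Put baseline in the outcome vector, for example with baseline means constrained equal across arms, so that women with only a baseline value stay in the analysis. Such women add little information on change, so the gain comes mainly from women with some follow-up.

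Keep the all-sessions analysis as a sensitivity analysis, and report attrition by arm, including the arms of the six women lost between randomization and baseline. A sensitivity analysis for data not missing at random, such as one in which dropouts follow the control trajectory, is optional.

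The cost is a change of wording, the MIXED procedure in the package already named, and slightly more analysis work. No new data are needed. The downside is reliance on a missing-at-random assumption, which should be stated.
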